| Effectiveness evaluation | 
① Primary efficacy measures
 
 
■ Oral clinical testing indicators: at screening periods, pre-treatment periods, and follow-up periods D90±3, D180±5, D360±5, examination was performed using a Florida probe, and the measurement of D90±3 was used as the evaluation endpoint.
 
■ attachment level AL (Periodontal depth PD + gingival recession GR).
 
 
② Secondary efficacy indicators
 
 
■ Imaging test indicators: at screening periods and follow-up periods D90±3, D180±5, and D360±5, examinations was performed using a Florida probe, and the screening periods was used as baseline, D180±5 measured value was used as the evaluation endpoint.
 
• Changes in periodontal defect height at 3, 6, and 12 months after the end of treatment compared with baseline (CBCT measurements, change of periodontal defect height = difference in distance from the cemento-enamel to the top of the alveolar ridge).
 
• Changes in mean alveolar ridge density at 3, 6, and 12 months after the end of treatment compared to baseline (CBCT measurements).
 
■ Oral clinical testing index: at screening periods and follow-up periods D90±3, D180±5, D360±5, using Florida probe for examination, use the measurement of D90±3 as the evaluation endpoint.
 
• PD compared to baseline;
 
• Periodontal healing compared to baseline (probing bleeding index BOP, gingival recession GR, tooth mobility TM).
 
 |

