| Statistical methods      | 
The phases of this study were randomized using block group randomization, with statisticians using SAS 9.4 software to generate random grouping codes. In Phase I, subjects were assigned in a 1:1 ratio according to the code to DPSCs injection group and saline injection group, and the randomization envelopes were recovered by the statistical management unit after the completion of this phase. In phase II, subjects were assigned to the saline injection group, single DPSCs injection group and double DPSCs injection group in a ratio of 1:1:3 according to the phase code. Statisticians were not involved in the screening, inclusion of subjects and subsequent clinical studies. The evaluators of the measurements were kept blinded during the study.
 
Statistical analysis datasets included the full analysis set (FAS), per protocol set (PPS), safety set (SS).
 
Analyses included subject distribution, balance analysis of baseline indicators, efficacy analysis, and safety analysis.
 
Means, standard deviations, medians, quartiles, minimum and maximum values were used for statistical description of measures, and ANOVA was used for comparisons between groups.
 
Statistical descriptions of count and rank information were made using rates or component ratios, and comparisons of count information were made using the <math>\chi^2</math> test or the Fisher exact probability method.
                                                                                                                    |

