| 2   | Inclusion /Exclusion Criteria                                                                                                     |                                                                                                                  | ×                           | ×                                      |                           |                                                           |                   |                   |                     |
| 3   | Demographic information                                                                                                           |                                                                                                                  | ×                           |                                        |                           |                                                           |                   |                   |                     |
| 4   | Medical history information                                                                                                       |                                                                                                                  | ×                           |                                        |                           |                                                           |                   |                   |                     |
| 5   | Vital signs: respiration, heart rate, blood pressure (systolic, diastolic), temperature (axillary), clinical condition assessment |                                                                                                                  | ×                           | × (Before / 2h±30 min after injection) |                           | × (Double DPSCs injection group 2h±30min after injection) |                   |                   |                     |
| 6   | Periodontal clinical indicators: AL, PD, BOP, GR, TM                                                                              |                                                                                                                  | ×                           | ×                                      |                           |                                                           | ×                 | ×                 | ×                   |

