### **4. Study steps:**

#### **(1) Screening Period (D-14~0):**

**【Signed Informed Consent Form】** : The investigator fully informs the subjects about the details of the study, the treatment options for chronic moderate periodontitis, possible risks and benefits. After obtaining a written, voluntarily signed informed consent form from the subject, the subject was included in the subjects screening.

**【Inclusion/exclusion criteria】** : Screening of subjects who meet the inclusion criteria and do not meet the exclusion criteria.

**【Demographic information】** : Demographic information of the subjects will be collected and recorded, including gender, date of birth, ethnicity, height, and weight.

**【Medical history】 :** Collect and record the subject's current medical history, allergy history, family history, antecedent history (smoking, diabetes, other surgical history, etc.).

**【Vital signs】 :** respiration, heart rate, blood pressure (systolic and diastolic), temperature (axillary), and clinical assessment of general condition.

**【Periodontal Clinical Indicators】 :** Periodontal examination was standardized using the Florida Probe of the Beijing Stomatological Hospital, Capital Medical University. Records: periodontal attachment level AL, periodontal probing depth PD, probing bleeding index BOP, gingival recession GR, tooth mobility TM, and the proposed treatment site (single tooth/subject) were selected by the investigator.

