## 2. Efficacy evaluation index

### (1) Primary efficacy measures

- **【Oral clinical testing indicators】** During the screening period, before administration, and follow-up period, D90±3, D180±5, and D360±5 were examined with Florida probe, and the measured value of D90±3 was used as the evaluation endpoint.  
Periodontal attachment level AL (PD+GR).

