#### **(1) Analyzed Population:**

Statistical analysis datasets for the study results included the full analysis dataset (FAS), the protocol compliance dataset (PPS), and the safety Sexuality dataset (SS).

**Full Analysis Set (FAS):** for all cases that had used the study drug after enrollment and had completed at least one efficacy assessment. cases with at least one efficacy assessment completed after enrollment. The estimation of missing values for the main indicators was performed by the method of LOCF (last observation carrying forward).

**Per Protocol Set (PPS):** a subset of the FAS, all cases that comply with the study protocol,

have good compliance, do not use prohibited drugs during the study period, have completed 6 months of clinical observation, and have completed the CRF;

**Safety Set (SS):** all cases that received the study drug after enrollment and had at least one safety assessment. Cases.

In this study, baseline information was analyzed using FAS and PPS analysis. Primary efficacy indicators, secondary efficacy indicators, etc. were analyzed by both FAS and PPS. However, the conclusions obtained from FAS analysis were the main conclusions. When the conclusions from FAS and PPS are consistent, the credibility of the conclusions can be increased.

In the safety analysis, adverse events and adverse reactions, vital signs, and laboratory indicators were analyzed using SS. subjects who were terminated prematurely due to adverse events and various non-therapeutic reasons were included in the safety analysis.

**(2) Statistical analysis plan:** the analysis of the study results included the description of the distribution of subjects, the balance analysis of baseline indicators, the analysis of efficacy, and the analysis of safety.

Mean, standard deviation, median, quartile, minimum and maximum values were used for the statistical description of the measurement data. Comparisons between groups were performed by ANOVA or Kruskal-Wallis rank sum test, and comparisons in groups were performed by paired t-test or Wilcoxon signed rank test. test for within-group comparisons.

Statistical descriptions of counts and rank data used rate or composition ratio, comparisons of count data used  $\chi^2$  test or Fisher's exact probability method, and comparisons of rank data used Kruskal-Wallis rank-sum test.

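### The stated between-group test for attachment level (AL) names no baseline covariate, so the day-90 comparison gives up precision that the pre-treatment readings could supply

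*Protocol*

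**What the plan says.** **Endpoint.** The synopsis (Effectiveness evaluation) gives the primary measure as "attachment level AL (Periodontal depth PD + gingival recession GR" and adds that "the measurement of D90±3 was used as the evaluation endpoint". Section (15), Primary efficacy measures, agrees: "the measured value of D90±3 was used as the evaluation endpoint". Neither place words AL as a change from baseline. The secondary probing and CBCT measures are worded as compared with, or changed from, baseline.

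**Test.** Synopsis, Statistical methods: "ANOVA was used for comparisons between groups". Section (XIX), Statistical analysis plan: "Comparisons between groups were performed by ANOVA or Kruskal-Wallis rank sum test". No covariate is named in either place. Section (XIX) also lists paired t and Wilcoxon signed rank tests within groups.

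**Baseline data.** AL is examined "at screening periods, pre-treatment periods, and follow-up periods D90±3, D180±5, D360±5". Section (V), Study steps, has it recorded at screening ("Records: periodontal attachment level AL, periodontal probing depth PD") and again at the D1 baseline/treatment visit. The schedule table marks "Periodontal clinical indicators: AL, PD, BOP, GR, TM" at both visits. For comparing the arms, both statistical sections mention baseline indicators only as the subject of a balance analysis.

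**Size.** Section (8) sets alpha 0.05 and power 0.80, combines the two stages for analysis, and expects about 33 saline, 33 single-injection and 30 double-injection subjects. It names S and delta but gives no value for either.

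**The concern.** Sites may enter with a probing depth anywhere from 4 to 8 mm, and AL contains probing depth. Some of the spread in day-90 AL is therefore spread that was already there before treatment. A comparison on group alone leaves that part in the error term, although the values that could remove it are collected on every subject.

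Two things are at stake with about 33 per arm. One is power for the primary comparison. The other is how the result reads if the arms happen to differ at baseline: a balance analysis can show such a difference but does not correct for it.

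The within-group paired tests do not fill the gap. They do not compare arms, and every arm receives scaling and root planing, so improvement within each arm is expected with or without cells.

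**Working it through.** **Inputs.** From Section (8): two-sided alpha 0.05, power 0.80, groups of about 33, 33 and 30. Not in the protocol, so assumed: the standardised effect delta/S, and the correlation rho between pre-treatment and day-90 AL, taken as 0.3 to 0.7.

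**Step 1: the protocol's own size.** The formula in Section (8) is n per group = 2[(t(1-alpha/2) + t(1-beta))S/delta]^2. Without S and delta, the total of 96 can be neither reproduced nor refuted. Solved backwards with normal quantiles, 32 per group implies delta/S = (1.96 + 0.84) x sqrt(2/32) = 0.70. The noncentral t distribution with 33 v 33 also gives 0.70. This value is used below as an assumption.

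**Step 2: power with and without baseline.** ANCOVA on one baseline reading reduces the residual SD to S x sqrt(1 - rho^2). The effect relative to residual SD becomes 0.70/sqrt(1 - rho^2), and n subjects do the work of about n/(1 - rho^2). Power is for a two-group comparison by noncentral t, with one degree of freedom less for the covariate.

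| rho | 33 works like | Power, 33 v 33 | Power, 33 v 30 |
|---|---|---|---|
| no adjustment | 33 | 0.80 | 0.78 |
| 0.3 | 36 | 0.84 | 0.82 |
| 0.4 | 39 | 0.86 | 0.85 |
| 0.5 | 44 | 0.90 | 0.88 |
| 0.6 | 52 | 0.94 | 0.93 |
| 0.7 | 65 | 0.98 | 0.97 |

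The 33 v 30 column is double injection against saline with the stages pooled, as Section (8) plans.

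**Step 3: if change from baseline was meant.** A change score has SD S x sqrt(2(1 - rho)). At rho 0.3, 0.5 and 0.7 that is 1.18 S, 1.00 S and 0.77 S, and 33 v 33 power is 0.66, 0.80 and 0.95. ANCOVA gives 0.84, 0.90 and 0.98. It does better than the day-90 value alone and better than the change score at each rho, and below rho 0.5 the change score is worse than the day-90 value alone.

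**Step 4: chance imbalance.** The SD of the difference in mean baseline AL between two arms of 33 is sqrt(2/33) = 0.246 baseline SD, so the 95% limit is 1.96 x 0.246 = 0.48 SD. The unadjusted day-90 difference moves by rho times that: 0.3 x 0.48 = 0.14 SD to 0.7 x 0.48 = 0.34 SD. Against an assumed effect of 0.70 SD, this is about 21% to 48%.

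Given an imbalance at that limit and no treatment effect, the unadjusted test statistic is approximately normal with mean 1.96 x rho and variance 1 - rho^2. The chance that it exceeds 1.96 in absolute value is about 8%, 13% and 21% at rho 0.3, 0.5 and 0.7, instead of 5%.

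**The case against.** **The form of the endpoint is not certain.** A reader might infer that the protocol fixes the unadjusted day-90 value as the endpoint. The wording does not settle this. The phrase about the evaluation endpoint is also applied to the CBCT measures, which are explicitly changes, so it may mark only the time point. Section (IV), Clinical indicators, expects AL to fall relative to pre-treatment. The day-90 value is the plainer reading because AL alone lacks baseline wording, but the ambiguity stands. It does not rescue the plan, since ANCOVA is also better than a change score.

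**Covariates are often left to a separate analysis plan.** That is true, and silence alone would be no finding. Here the protocol names the test in two places, so naming a better one improves a stated choice.

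**Nothing stated is invalid.** This stands. A reader might infer that the planned comparison is biased or has an inflated error rate. It does not: over randomisations it is unbiased and holds overall alpha. The error rates in Step 4 apply only conditionally on an imbalance of the stated size. The study is also labelled exploratory.

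**The size rests on assumptions.** This stands too. The effect size is back-solved, rho is assumed, and the 4-8 mm entry range may lower rho by restricting the spread. At rho 0.3 the gain is about 4 points of power.

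**Adjustment for phase is a different matter.** Double injection exists only in the second stage, so a phase term costs precision in the double-versus-saline contrast. With a phase term, power at delta/S 0.70 would be 0.60 before baseline adjustment. A reader might take 0.60 as the starting point and credit the whole rise above it to baseline adjustment. The protocol pools the stages, so its starting point is 0.78.

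**Conclusion.** The point holds as a free improvement to a valid analysis. The protocol names ANOVA or Kruskal-Wallis without a covariate, while pre-treatment AL at the treated tooth is already collected twice.

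On the assumptions above (delta/S 0.70, rho 0.3 to 0.7), baseline adjustment adds about 4 to 18 points of power for 33 v 33 and 4 to 19 points for pooled 33 v 30. It also removes a possible shift of 0.14 to 0.34 SD in the day-90 difference when baseline imbalance reaches its 95% limit. The direction does not depend on the exact rho, provided that pre-treatment and day-90 AL are appreciably correlated; the size does.

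Whether to adjust for phase is a separate question of bias. Its cost in precision should not be counted in the gain given here.

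**What to change.** 1. In the synopsis (Statistical methods) and in Section (XIX), name ANCOVA of day-90 AL on pre-treatment AL and treatment as the primary between-group analysis. Report adjusted differences with 95% confidence intervals.
2. State whether the AL endpoint is the day-90 value or a change from baseline. With pre-treatment AL in the model, the estimated treatment difference is the same either way.
3. Name one pre-treatment reading as the probing baseline. The D1 reading is available and precedes injection.
4. Reconcile the synopsis with Section (15) for the secondary probing measures: the synopsis lists only screening before follow-up, while Section (15) also lists a pre-administration reading.
5. Apply the same model to PD and GR with the probing baseline, and to the CBCT height and density measures with their stated screening baseline.
6. Keep the within-group tests descriptive.

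The cost is wording only. No new visits, measurements or subjects are needed.

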### **(I) Research Title**

Clinical Study of Allogeneic Human Pulp Stem Cells in the Treatment of Chronic Periodontitis (A randomized, open, controlled clinical study of periodontal basic therapy combined with human pulpal mesenchymal stem cell injections for the treatment of chronic moderate periodontitis).

### **(II) Objectives of the study**

- (1) To evaluate the safety and efficacy of human DPSCs injection in the treatment of chronic moderate periodontitis;
- (2) To provide a basis for the development of a standardized clinical protocol for the treatment of chronic moderate periodontitis with DPSCs injection.

### **(III) Basis of the project**

Periodontitis is a progressive and destructive disease caused by bacterial infection that occurs around the natural teeth as a supportive tissue and is one of the most common chronic diseases of the oral cavity, with a prevalence of up to 90% in China. It is characterized by soft tissue inflammation, periodontal pocket formation and alveolar bone resorption, resulting in insufficient supportive hard tissues around the teeth, progressively loosening and displacing of the teeth, and eventually loss. Periodontitis has been called the "incurable disease" of dentistry, is not only the first cause of tooth loss among adults in China, but also increases the risk of cardiovascular disease, diabetes and rheumatoid arthritis. The ultimate goal of periodontitis treatment is the regeneration of periodontal tissues (alveolar bone, periodontium, osteoid, and gingiva), and the regeneration of functional periodontal tissues is the focus and difficulty of clinical periodontitis treatment. At present, conventional clinical treatments such as basic periodontal therapy, periodontal surgery (periodontal flap surgery, guided bone regeneration, guided tissue regeneration) are difficult to achieve satisfactory tissue regeneration. In recent years, the rapid development of stem cells and tissue engineering has provided an opportunity for periodontal regeneration, the rapid development of stem cells and tissue engineering has provided new ideas for periodontal regeneration, among which mesenchymal stem cells (MSCs) are widely available and easy to culture and expand in vitro. MSC can not only secrete a variety of bioactive molecules, including immunomodulation, anti-apoptosis, anti-inflammation, anti-fibrosis, and pro-angiogenesis, but also chemotaxis to tissue trauma and inflammation sites, these characteristics make MSC widely used in regenerative medicine research, as of July 2019, as many as 972 clinical therapeutic studies of MSC have been conducted worldwide, and there are clinical trials registered for bone marrow mesenchymal stem cells and oral mucosal stem cells for periodontal tissue regeneration research and periodontal disease treatment research (<https://www.clinicaltrials.gov/>). In China, many hospitals have started MSC treatment for immune disorders and degenerative and injurious diseases. These studies have demonstrated a very good safety profile in the application of MSC for the treatment of localized tissue lesions or systemic diseases.

This project has developed DPSCs injection which can regenerate periodontal tissue and form new periodontal attachments for periodontitis treatment, clinical studies have shown that DPSCs injection are effective in repairing periodontal defects based on their multidirectional differentiation and immunomodulatory abilities. We retrospectively analyzed the data of 18 subjects from two non-registered clinical trials. 18 subjects with chronic moderate periodontitis who were enrolled in two non-registered clinical trials and completed basic periodontal scaling combined with a single topical cellular injection, of which 18 subjects were analyzed for safety and 14 subjects with follow-up data were included in the effectiveness analysis. The results of the study showed:

- (1) No serious adverse events or adverse reactions occurred in the 18 subjects during the trial period, and no subjects withdrew from the trial because of adverse events or adverse reactions. The subjects received  $1 \times 10^7$ - $8 \times 10^7$  cell doses of DPSCs injection locally after basic periodontal treatment, no adverse reactions were observed.
- (2) In a randomized controlled study of 10 cases, the periodontal soft tissue recovery in the basic periodontal therapy combined with DPSCs injection group was better than saline group. In the saline group, 2/5 subjects had mild redness, swelling of the gums and multiple bleeding on probing on the 90th day after treatment, while in the DPSCs injection group, 5/5 subjects had no further gingival redness, swelling, or bleeding on probing until the end of the follow-up period (18/24 months).
- (3) No tumor development was observed in any of the 18 subjects, including: no tumor development was observed in the 8 open study subjects who were followed up by telephone 48 months after administration of the drug; and no tumorigenic risk was observed in the 10 randomized controlled study subjects who were tested for blood tumor markers at 18/24 months, no tumorigenic risk of DPSCs injection.
- (4) An analysis of the effectiveness of the 14 subjects showed that the clinical efficacy of periodontal basic therapy + DPSCs injection group was superior to that of periodontal basic therapy + untreated / saline injection group: ① the patients' periodontal attachment level AL improved, and compared with saline injection group, there was a significant improvement in the AL values after 3 months of DPSCs injection. ② the periodontal probing depth PD of the patients improved in both group, and DPSCs injection group showed significant improvement in PD values at 3 and 6 months after treatment compared with saline injection group.

Therefore, this project proposes to further evaluate the safety and effectiveness of DPSCs injection in the treatment of chronic moderate periodontitis, and to provide a basis for the development of clinical standardized protocols for the treatment of chronic moderate periodontitis with human dental pulp mesenchymal stem cells.

